## Abstract

(1) Background: Antibiotic resistance is an imperative public health issue globally. Major factors that are resulting in this trend are the irrational and excessive use of antibiotics. Children account for a greater population of antibiotics use, therefore, an educational intervention on the rational use of antibiotics for children and caregivers will be beneficial. (2) Methods: A randomized controlled and parallel group study of fifth grade children and their caregivers will be evaluated in four primary schools in Baoji and Weinan of the Shaanxi Province. Two primary schools will be randomly selected for the educational intervention and two schools will serve as a control group. In the intervention arm, educational interventions will be conducted among caregivers and their children. The intervention measures include interactive training sessions, booklets, and printed or electronic educational materials that will be given to the caregivers or the school-aged children. In the control arm, no interventions will be implemented. Baseline data collected from June, 2018 and the intervention will last for three months. Knowledge-Attitude-Practice (KAP) questionnaires will be used to evaluate the caregivers’ knowledge, their attitude, and their practice. Knowledge-Retention questionnaires will be used to assess the children’s knowledge about microbes, antibiotics, and hygiene. (3) Discussion: This study is a unique comprehensive intervention targeting both children and their caregivers. We hypothesize a decrease in the irrational use of antibiotics among the studied population. Hence, this result would provide evidence for policy makers and educational departments for the implementation of similar interventions on the rational use of antibiotics.

## 1. Introduction

Antimicrobials are considered as one of the greatest inventions of the twentieth century [1]. Since their advent, they have been widely used in clinical practice and have played a great role in preventing and treating the infectious diseases of humans [2,3]. Currently, they account for the most consumed medicines worldwide [4], and the issue of bacterial resistance due to their overuse is a pressing global health concern [5,6,7]. There is a direct correlation between antibiotics abuse and the emergence of bacterial resistance, which increases the risk of adverse reactions and disease burden on the health system [8,9,10]. There has being a global drive towards research on this issue from key research and health promoting institutions in recent times. In 2010, the “Lancet” reported on “super bacteria” that can resist almost all antibiotics [11], and the 2011 theme of World Health Day was to Combat drug resistance—No action today, no cure tomorrow [12]. In 2014, a global antibiotic resistance monitoring report found that antibiotic resistance exists in all regions, revealing that at any time, the world will reach the “post-antibiotics” era [13], and in 2015, reports in China showed that the detection rate of methicillin-resistant Staphylococcus aureus (MRSA) was 35.8% and that the detection rate of erythromycin-resistant Streptococcus pneumoniae was 91.5% [14].

Children account for a greater proportion of antibiotics use in China, especially for upper respiratory tract infections in which it is common for them to be given antibiotics [15,16]. Even though these infections are mostly viral in nature [17,18] and there is evidence-based clinical guidelines pinpointing their ineffectiveness against colds, coughs, and sore throats, which are all of the most common respiratory tract infections [19,20], many caregivers still expect doctors to prescribe antibiotics for their children [21,22,23]. This practice has resulted in adverse events and health consequences in the population [24]. For example, a study in China on childhood deafness amongst children under the age of seven showed that the unreasonable use of antibiotics accounted for 30% to 40% of all cases, while in some developed countries it only accounted for 0.9% [25]. It has also been reported that the use of antibiotics in children is closely associated with their caretakers’ cognition, concepts, and habits about antibiotics [26]. In their study, using the Knowledge, Attitude, and Practice (KAP) questionnaire, Panagakou SG et al. [27] reported that although 80% of parents think that upper respiratory tract infections are viral infections, 74% of parents still expect their children to be treated with antibiotics.

In response to the irrational use of antibiotics in children, the majority of studies have focused on educational intervention to improve the knowledge about antibiotics in both children and caregivers [28,29,30,31,32,33,34]. Numerous studies [35,36,37] have shown that health educational intervention is an important method that can be used to promote the rational use of antibiotics. Some of these interventions are in the form of: professional education, training programs, seminars, publicity, educational materials, and face-to-face education for health service providers, patients, the general public, caregivers, policy makers, and so on [38]. In order to promote the rational use of antibiotics in children, children and their guardians need to work together. From the perspective of children, schools are one of the main crowded places and infectious diseases are easily transmitted among students. Therefore, educating students to prevent the spread of infectious diseases and decreasing the incidence of infectious diseases in children can reduce the use of antibiotics. In addition, children are a new generation of antibiotic users and may be future prescribers, therefore their awareness of rational use of antibiotics from a young age will have long-term effects. From the perspective of caregivers, the expectations of caregivers has a great impact on doctor’s antibiotic prescribing patterns for children. Therefore, improving knowledge about rational antibiotic use among caregivers is important for the well-being of children. Gaps exist in the literature on educational intervention studies targeting both children and their caregivers in China, hence, our study will attempt to fill such gaps and if the feasibility of the delivery of such interventions can be demonstrated, future studies will be able to investigate using our protocol as a model. Therefore, we conduct this research with the aim to assess the effectiveness of an educational intervention to improve school-aged children’s knowledge about hygiene and antibiotic use and caregivers’ knowledge, attitude, and practice about the rational use of antibiotics for children. In addition, we will try to elicit the knowledge, attitudes, and practice patterns of caregivers who are using antibiotics for children and will disclose knowledge about hygiene and antibiotic use among school-aged children. 

## 2. Materials and Methods

### 2.1. Study Design

We will conduct a multistage cluster randomized controlled trial at the school-level. Our study will be carried out in primary schools in the Shaanxi Province, western China. According to the economic level of the Shaanxi Province, two clusters were formed: developed areas, where we chose Baoji, and Weinan from the less developed areas. The chosen primary schools from both of the study sites met the following inclusion criteria: (1) Schools must be willing to take part in our study; (2) Schools should be in urban areas with enough teachers and students. In rural areas, most young people need to go out to work and earn a living, leaving the elderly to look after the children. Socio-demographic characteristics are quite different between rural and urban areas, so we only include urban primary schools. (3) Schools are theoretically matched and are comparable with each other in terms of school size and teaching level; (4) Must be public primary schools because private primary schools are mainly composed of students with higher family incomes. (5) Two schools in each city must be in different districts or in different streets. The distance between the two schools in each city must be more than 5 km. Based on the inclusion criteria and the referenced CONSORT (Consolidated Standards of Reporting Trials) statement for randomized trials [39], a final selection of two primary schools in each city will be made. In total, there are 804 public primary schools in Baoji and 638 public primary schools in Weinan. Among these schools, in Baoji there are 37 schools in urban areas and 767 in county or in rural areas. For the schools in urban areas, 10 schools are unwilling to participate in our study and 17 schools are small scale (which have less than three classes in the fifth grade or less than 1500 students in schools). Taking the distance between the two schools in the same city into account, we chose two schools from the remaining 10 schools. In Weinan, there are 23 schools in urban areas and 615 in counties or in rural areas. The sampling process was similar in Weinan and we have depicted it in Figure 1 (The sampling process). In each city, one primary school will be randomly selected for the intervention group and the other will serve as the control group. The study participants will be chosen from the class level and in every school we will select three to five classes from the fifth grade at random. Participants will be selected based on the inclusion criteria from the chosen classes and they will be blinded on their assigned group.

This study will be divided into three phases: pre-intervention, intervention, and post-intervention. In the pre-intervention phase, we will administer the KAP questionnaire and the Knowledge-Retention questionnaire to the caregivers and children to collect baseline data. Baseline data will be collected from June 2018. After baseline data is collected, we will implement health education interventions for the children and guardians, respectively, and it will last for three months. Immediately after the intervention, we will send questionnaires to the studied groups, that is, the children and caregivers. However, for school-aged children, we will again send the Knowledge-Retention questionnaire to them to evaluate the retention of knowledge one month after the intervention. Pre and post-intervention data will be compared between the intervention and the control groups, and we will then analyze the results to assess the impact of the interventions on antibiotics use among children.

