### 2.2. Sample Size

Based on the previous study [40], the rate of irrational use of drugs by guardians for their children is 40% to 70%. Through our educational intervention, we hypothesized a 15% reduction in the rate of irrational drug use among children. We set α = 0.05, 1 − β = 0.9. We used software, Sample Size 2.0, to calculate the sample size, and 231 participants are required for the intervention and control groups. Taking into account the lost population, the invalid questionnaires, and the low response rate, we increased the sample size by 55%, to a total sample size of 720. We will select 180 school-aged students in every school. For each child included in our study, we will also invite their caregiver to participate in the study. In four primary schools, we chose 720 students and 720 caregivers. The sampling process is shown in Figure 1. We also invited teachers to help us to do our study. They are the bridge of communication between researchers and caregivers. Caregivers may not follow the orders from researchers, however most parents will follow tasks that are assigned by the teacher and, therefore, we will invite teachers to help us to implement a smooth intervention. In addition, they will help the researchers to distribute and collect the questionnaires from the children and caregivers. Before the intervention, we will give training to the teachers so that they will know more about our study and will clearly know their duty. In each class, we will invite 1 head teacher to cooperate with us.

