### 2.3. Eligibility Criteria for Participants 

We will include healthy children (aged 8–12) and caregivers who have the primary responsibility for the children and have normal understanding, cognitive, and communication skills.Children and caregivers who volunteer to participate in this study must have lived in the sample area for more than a year and those with less mobility will be included. A written informed consent will be collected from all of the participants.We will exclude children with severe liver, kidney disease, chronic diseases, and severe syndromes.We will preclude caregivers who work in the health field.

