### 2.8. Ethical Considerations

Before conducting this research, some ethical issues need to be considered. An informed consent form and other research-related documents were reviewed and approved by the Research Ethics Committee of Xi’an Jiaotong University (Ethical Code: 2018-451). We will obtain a written informed consent form from the participating children and guardians, in which the purpose of the study and their role in the study will be stated. The information will be stated verbally or written in a comprehensible way. There are two copies of the informed consent forms of which participants will keep one of them. They can also ask for details about the study and can make suggestions. It is voluntary to participate in the study and the participants are free to withdraw at any stage. Each participant will be allocated a unique identification number. We will inform participants that their information may be used for research purposes only and confidentiality will be guaranteed. All of the data will be stored in a safe place, accessible only to key researchers. Personally identifiable information such as the name or address of a participant will not published in any paper or documents. 

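### As section 2.1 describes it, schools are allocated before families are selected and consented, with no stated blinding of recruiters, so who enrols can differ by arm

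*Protocol article*

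**What the plan says.** Section 2.1 (Study Design) states the unit of randomisation: "We will conduct a multistage cluster randomized controlled trial at the school-level". There are two schools in each of two cities, and the steps then appear in this order:

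1. Allocation: "In each city, one primary school will be randomly selected for the intervention group and the other will serve as the control group".
2. Class sampling: "in every school we will select three to five classes from the fifth grade at random".
3. Participant selection: "Participants will be selected based on the inclusion criteria from the chosen classes and they will be blinded on their assigned group".

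Other sections bear on who enters:

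- Section 2.3 makes entry voluntary: "Children and caregivers who volunteer to participate in this study must have lived in the sample area for more than a year".
- Section 2.8 requires individual written consent, "in which the purpose of the study and their role in the study will be stated".
- Section 2.2 invites a caregiver for each included child, uses teachers as the link to caregivers, and allows for poor participation: "Taking into account the lost population, the invalid questionnaires, and the low response rate, we increased the sample size by 55" per cent, giving 720.
- Section 2.4 gives the intervention arm a 1.5-hour session in each of three months, a booklet to study and WeChat material that must not be shared. The control arm gets none of this.

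Section 2.1 also has baseline questionnaires in both arms before the intervention and a comparison of pre and post data between arms. The Discussion presents that comparison as the way to obtain the net effect.

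**The concern.** Randomising schools makes the arms comparable only in the pupils and caregivers who could be enrolled. If families are identified and consented after the arm is known, enrolment itself can depend on the arm.

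The conditions for this are present. Entry is by volunteering. What is asked of families differs greatly between arms. The Discussion itself says that the time demands of an intervention study make recruitment harder than for a cross-sectional study, and from a control family's side this trial is close to a survey. Better-informed or more motivated caregivers could then be over-represented in one arm. With only two schools per arm, such a difference is also mixed with ordinary differences between schools.

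At stake is the comparability of the arms on the caregivers' primary outcome, the proportion using antibiotics irrationally, and on how ready the enrolled families are to change.

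**Working it through.** **The plan's own figure.** Section 2.2 gives a rate of 40% to 70%, a 15% reduction, α = 0.05, power 0.90 and 231 participants. Taking the midpoint 55% against 40%, two-sided, with pooled variance and no continuity correction:

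n = [1.960 × √(2 × 0.475 × 0.525) + 1.2816 × √(0.55 × 0.45 + 0.40 × 0.60)]² / 0.15²
= (1.384 + 0.895)² / 0.0225 ≈ 230.8, so 231 per group.

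Then 2 × 231 × 1.55 = 716, close to the stated 720. The figure reproduces, with 15% read as percentage points, and this point does not change it. The allowance for loss, invalid questionnaires and low response together is 720 − 462 = 258, or 36% of 720.

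**Order of steps.** The table sets the text against what would protect recruitment.

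| Safeguard | What the article says |
|---|---|
| Consent before the draw | Not stated; selection follows allocation in 2.1 and refers to a group already assigned |
| Baseline before the draw | Not stated; 2.1 puts baseline before the intervention only |
| Recruiters blind to arm | Not stated for researchers or teachers |
| Classes chosen at random | Stated; prevents picking of classes, not selective volunteering within them |
| Participants blind to arm | Stated; hard to reconcile with 2.8 (role disclosed at consent) and 2.4 (one arm untreated) |

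**Illustrative size.** Assumptions, none of them in the documents except the 40% to 70% range: the true irrational-use rate p is equal in both arms; consent is unrelated to use in the control arm; in the intervention arm irrational users consent at r times the rate of others.

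Enrolled rate in the intervention arm = p·r / (p·r + 1 − p). Baseline gap = p − enrolled rate.

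With p = 0.55:

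| r | Enrolled rate | Gap (points) |
|---|---|---|
| 0.95 | 0.5225 / 0.9725 = 53.7% | 1.3 |
| 0.90 | 0.495 / 0.945 = 52.4% | 2.6 |
| 0.80 | 0.440 / 0.890 = 49.4% | 5.6 |
| 0.70 | 0.385 / 0.835 = 46.1% | 8.9 |

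The result depends little on p. At r = 0.70, p = 0.40 gives 0.40 − 0.28/0.88 = 8.2 points, and p = 0.70 gives 0.70 − 0.49/0.79 = 8.0 points.

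These are gaps at baseline. A comparison that uses the baseline would remove part of them. It would not remove a difference in readiness to change, because that acts on the before-to-after change itself. The documents give nothing from which to put a size on that part.

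**The case against.** The strongest reply is that the order is inferred. The article nowhere dates the draw relative to consent. The sentences of 2.1 are in the future tense, Figure 1 (the sampling process) is not shown here, and a journal article may leave the timing of allocation to the full protocol. This stands as a limit on certainty: the point concerns the sequence as described, not a demonstrated fact about conduct. But step order is something 2.1 does set out, and nothing in the article points the other way.

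Second, participants are said to be blind to their group, and families who did not know their arm could not volunteer differently because of it. That safeguard deserves credit, as does random class selection. It covers participants only, and it sits poorly with a consent form that states their role.

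Third, a reader might infer that recruitment bias here could not be told apart from a real effect, or might set the gaps above against the 15-point target or turn them into a false-positive rate. The documents do not support that. Baseline questionnaires are taken in both arms, and pre and post data are compared between arms, so a gap in baseline use would be visible and partly removed. A false-positive rate computed from these gaps would assume a post-only comparison, which is not what 2.1 and the Discussion describe.

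Fourth, some of the supporting evidence is modest. The low response in 2.2 may mean questionnaire return rather than refusal of consent. Teachers are trained before the intervention, which need not mean before recruitment, and no section gives them a part in selecting or consenting families.

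**Conclusion.** The point holds as a design weakness worth correcting. Followed in its described order, the plan allocates schools first and enrols volunteers afterwards, and states no blinding of those who approach them. The two stated safeguards narrow the route to recruitment bias but do not close it.

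Under assumed consent ratios of 0.95 to 0.70 and a true rate of 55%, the baseline gap is about 1 to 9 points. This shows what selective volunteering could do to the enrolled groups. It is not the bias in a baseline-adjusted effect, and it is not evidence that such bias will occur. What the planned comparison cannot repair is a difference between arms in motivation to change, and that remainder has no size that the documents allow one to compute.

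If consent and baseline were in fact completed before the draw, the point is settled by saying so.

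**What to change.** Reorder 2.1 as follows:

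1. In both schools of each city, sample the classes, obtain consent with the same wording in every school, and complete the baseline questionnaires.
2. Only then draw which school receives the intervention. The draw should be made by a person with no part in recruitment.
3. Report the numbers eligible, approached and consented for each school.

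If consent already precedes the draw, one sentence in 2.1 is enough. Baseline already comes before the intervention, so the change mainly moves the draw later.

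The cost is small but not zero. Trainers and teachers learn the allocation later and have less time to prepare. A common consent text that spelled out the intervention would tell control families what it contains, which works against the participant blinding in 2.1 and the contamination concern in the Discussion. The text should therefore describe the arms only in general terms.

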### 2.4. Intervention Procedures

The purpose of the intervention is to change the knowledge, attitude, and behavior of guardians about the use of antibiotics for children with upper respiratory tract infections and, at the same time, to improve children’s knowledge about antibiotics use and to help them build awareness of preventing infection. We have created a WeChat (the most popular web-based social media tool in China) official account, through which we will push educational materials about the rational use of antibiotics to guardians. Only participants in the intervention group will have access to the information in the WeChat platform. Besides, participants are required to not share the information to others during the intervention period. For those caregivers who do not have WeChat accounts, we will distribute paper education materials separately, which will be the same as the electronic one. The educational materials are from the Center for Disease Control and Prevention in America [41]. Under the circumstance of China, we will translate the educational materials into Chinese and will make them easy to understand. We developed booklets about rational antibiotics use in children which cover the basic concept of antibiotics, antibiotic resistance, bacterial and viral infections, indications of antibiotics, and problems that can be encountered with the use of antibiotics and so on. The booklets will be taken home by the students. Both the students and the caregivers are required to study the booklet with commands from the teachers. Additionally, every month within a 3-month period, experts in the field will conduct a 1.5-h interactive training session for the children and their caregivers, and before each training session, we will issue them with the teaching materials. The content of the training session mainly includes four aspects: knowledge on microorganisms, the spread of infection, the prevention of infection, and the rational use of antibiotics for respiratory diseases. However, the training session for the caregivers will focus on the rational use of antibiotics and that for the children will concentrate on the knowledge of microorganisms, the spread of infection, and the prevention of infection. In the control group, both the children and caregivers will have no access to any intervention measures.

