### 2.6. Data Management 

During the period of pre-intervention and post-intervention, we organized the children and their guardians to complete the knowledge retention questionnaire and the KAP questionnaire, respectively, and for the illiterate participants, the researchers will read and explain the content of the questionnaire to them. Two different tools are used in this study: a knowledge retention and KAP questionnaire. Both questionnaires were developed based on published literatures [42,43,44,45,46] and were issued to the children and caregivers in one class before the study. According to the opinion of the children and caregivers, we revised the language of the questionnaire to ensure that the respondents can correctly understand the meaning of each item. In brief, the knowledge retention questionnaire has a total of 26 structured or semi-structured questions which can be divided into five sub sections: (1) Knowledge related to microbes, including differences between bacteria and viruses, and differences between bacterial infections and viral infections. (2) Hand hygiene, including the importance of washing hands frequently, when hands should be washed, and how to wash hands. (3) Respiratory hygiene, including the spread of infectious diseases through coughing or sneezing, and how to prevent the spread of bacteria when sneezing. (4) Food hygiene, including the problems of food contamination and cross-contamination and disposing leftovers and deteriorated foods. (5) Knowledge related to antibiotics, including the basic concepts of antibiotics and indications for antibiotic use, etc. The KAP questionnaire for the caregivers consisted of 30 structured or semi-structured questions, and is divided into four parts: (1) The demographics of the caregivers, including gender, age, educational level, family income, health insurance, and the relationship between the guardians and the children. (2) The knowledge part is to assess the guardian’s cognition of antibiotic-related knowledge, including the relationship between antibiotic use and drug resistance, and the indication of antibiotics. (3) The attitude part includes whether they agree that the use of antibiotics in advance can prevent diseases such as colds, whether children should get antibiotics immediately if they have respiratory tract infections, whether using antibiotics can speed up the recovery of colds and coughs, whether expensive antibiotics are better than cheap ones, and whether caregivers should gain more knowledge about antibiotics, etc. (4) The behavioral part evaluating the behavior of the guardians using antibiotics for their children includes whether they stored antibiotics that were needed by children at home, whether they used antibiotics that were stored at home or the remaining antibiotics, whether they changed the dosage of antibiotics according to the condition of children, and whether they took the initiative to ask doctors to prescribe antibiotics, etc. After the intervention, an evaluation component is added in the KAP questionnaire among the participants in the intervention group, which consists of 12 questions and is intended to evaluate whether the intervention population are satisfied with the intervention measures. Both of the data collection tools were developed after extensive literature searches of related studies and after consulting with experts on infectious diseases in children. All researchers will have a uniform training before the questionnaire is issued to be very familiar with each item in the questionnaire. Once the participants complete the questionnaire, they will be collected by the researchers and will be kept in good condition. We will screen and rule out invalid questionnaires in which the key information is incomplete and is filled out arbitrarily.

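### Participants are described as blinded, but intervention families cannot be once the intervention starts, so differential reporting could mimic benefit on the self-reported caregiver primary outcome

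*Protocol article*

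**What the plan says.** **Blinding.** Section 2.1 (Study Design) says: "Participants will be selected based on the inclusion criteria from the chosen classes and they will be blinded on their assigned group". The sentence sets no time limit and names no arm.

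**What the arms receive.** Section 2.4 (Intervention Procedures) gives booklets to the intervention families and says: "Only participants in the intervention group will have access to the information in the WeChat platform". It adds that "participants are required to not share the information to others during the intervention period". In each of three months, "experts in the field will conduct a 1.5-h interactive training session for the children and their caregivers". For the comparison arm: "In the control group, both the children and caregivers will have no access to any intervention measures". The Discussion adds reminder messages and sign-in for the sessions.

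**The outcome.** Section 2.5 makes the caregiver primary outcome the proportion who use antibiotics irrationally for their children, defined by a list of behaviours of which any one suffices. The KAP questionnaire measures it, and no source other than the caregiver's answers is described. Section 2.1 places the post-intervention questionnaire directly after the intervention ends.

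**Who handles the forms.** Section 2.4 says: "Both the students and the caregivers are required to study the booklet with commands from the teachers". Section 2.2 says of the teachers that "they will help the researchers to distribute and collect the questionnaires from the children and caregivers", whereas Section 2.6 (Data Management) names the researchers as the collectors.

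**The form.** Section 2.6 says: "After the intervention, an evaluation component is added in the KAP questionnaire among the participants in the intervention group". This component has 12 questions on satisfaction with the intervention.

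**The concern.** A reader who takes the blinding statement at face value would discount reporting bias in the caregiver primary outcome. That is the bias to which this outcome is most exposed. Intervention caregivers report on keeping, reusing or adjusting antibiotics just after being taught that these are wrong. The forms pass at least partly through teachers, whom Section 2.2 enlists because parents tend to do what teachers ask.

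If intervention caregivers then under-report more than control caregivers, the trial will show a reduction in irrational use that is partly or wholly a change in answers. The Discussion says that a control group with before-and-after data gives the net effect, but that comparison does not cancel a reporting shift that arises after exposure and differs by arm. The Discussion considers contamination, non-attendance, short duration and generalisability, but not reporting bias.

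**Working it through.** **1. Can the blinding statement hold?**

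| Feature | Intervention | Control | Section |
|---|---|---|---|
| Training sessions | monthly for 3 months, with sign-in | none | 2.4, Discussion |
| Booklet | yes, study directed by teachers | none | 2.4 |
| WeChat account | access | no access | 2.4 |
| Non-sharing instruction | yes | nothing to share | 2.4 |
| 12 satisfaction questions | yes | no | 2.6 |

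There is no sham or attention control. A caregiver who attends sessions, is told not to pass the material on and then rates it knows that an intervention was received. The statement can hold at selection and at baseline, and perhaps for control families throughout. It cannot hold for intervention families at the post-intervention measurement.

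**2. The plan's own figure.** Inputs from Section 2.2: irrational use 40% to 70%, a 15% reduction, α = 0.05, power 0.90. Sidedness is not stated; two-sided reproduces the figure. Take p1 = 0.55 (the midpoint) and p2 = 0.40, so the mean is 0.475:

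n = [1.960 × √(2 × 0.475 × 0.525) + 1.282 × √(0.55 × 0.45 + 0.40 × 0.60)]² / 0.15² = 230.8, so 231 per group.

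This matches the stated 231, and 2 × 231 × 1.55 = 716 is close to the stated 720. The target is therefore a 15-percentage-point difference, and no stated figure is wrong on this point.

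**3. How reporting passes through the comparison.** Let p be the true rate in both arms at both times (no true effect). Let a fraction g of irrational users under-report at baseline in both arms and in control afterwards, and a fraction f in the intervention arm afterwards.

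- Intervention change: p(1 − f) − p(1 − g) = −p(f − g)
- Control change: 0
- Difference in changes: −p(f − g)

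Only the excess f − g matters, and subtracting baseline does not remove it.

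**4. Size.** The documents give neither f nor g, so both are assumptions. With g = 0, the value of f that creates the full 15 points is 0.15/p:

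- p = 0.40: 0.15/0.40 = 37.5%
- p = 0.55: 0.15/0.55 = 27%
- p = 0.70: 0.15/0.70 = 21%

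Smaller values at p = 0.55, with the chance of a significant difference in a simple two-proportion test that ignores clustering:

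| f | Apparent difference (points) | 231 per arm | 360 per arm |
|---|---|---|---|
| 10% | 5.5 | 22% | 31% |
| 20% | 11.0 | 66% | 84% |
| 30% | 16.5 | 95% | 99% |

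At f = 20% with 231 per arm, the chance is 43% for p = 0.40 and 88% for p = 0.70. A larger sample makes the false result more likely to reach significance.

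**The case against.** The strongest reply is that the blinding sentence concerns selection. Participants may well be unaware of their group when chosen and when they complete baseline forms, and control families, at a school more than 5 km away and without WeChat access, may remain unaware. This reading is possible, but the text does not limit itself to it, and it gives no protection at the post-intervention measurement, where the effect is estimated.

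Other replies stand in part:

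- **Teachers.** Experts run the sessions, teachers only help with the forms, and Section 2.6 names researchers as collectors. Section 2.8 promises ID numbers, confidentiality and data access for key researchers only. This softens the concern, but does not say that teachers will not see caregivers' answers, and Sections 2.2 and 2.6 still need reconciling.
- **The composite outcome.** A caregiver with several irrational behaviours must deny all of them to be reclassified. So f is the share reclassified altogether, not the under-reporting on a single item.
- **The children's primary outcome.** It is correct answers to knowledge questions and is not threatened in the same way.

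A reader might also infer more than the documents support:

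- That biased answering happens in the intervention arm only. Control caregivers may also shade their answers, and one head teacher is invited in every class. A larger effect in the intervention arm is probable, not shown.
- That the outcome items differ by arm. The plan only adds a satisfaction component; it neither changes the outcome items nor says where the added questions stand.
- That consent reveals allocation. Section 2.8 says that purpose and role are stated, not the assigned group.
- That help for illiterate participants favours one arm. It is not restricted by arm.

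**Conclusion.** The point holds for the caregiver primary outcome. The unqualified blinding statement contradicts the plan's own procedures from the start of the intervention onward, and the outcome is self-report taken straight after teaching. Differential reporting could therefore mimic benefit, and the controlled before-and-after comparison would not remove it.

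The contradiction is certain; the size of the bias is not. Under-reporting of 37.5%, 27% or 21% at baseline rates of 40%, 55% or 70% equals the whole planned effect, assuming no true effect and no under-reporting in control. Under-reporting in control would shrink the bias to the excess in the intervention arm. The documents do not show that any such reporting will occur, and nothing here means that an observed benefit would be false.

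**What to change.** 1. In Section 2.1, delete the blinding statement or restrict it to selection and baseline, and state that participants and teachers are unblinded afterwards.
2. Reconcile Sections 2.2 and 2.6 on who collects the questionnaires. Have caregiver forms returned sealed and marked with the ID number only, so that teachers who help do not see the answers.
3. In Section 2.6, use the same KAP outcome form in both arms and give the 12 satisfaction questions on a separate sheet after it has been handed in.
4. In the Discussion, state reporting bias as a limitation on the caregiver primary outcome, and qualify the claim that the comparison gives the net effect.

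The cost is envelopes, one extra sheet, some rewording and a more cautious conclusion. No added staff and no change to the sample size are needed. These steps reduce the bias but do not remove it, because intervention caregivers will still know what they were taught.
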